## Abstract

This project will investigate the effectiveness of an 8-week outdoor fitness equipment (OFE) programme on health parameters in healthy community-dwelling middle and older adults, corresponding to the present paper to the study protocol, which follows a single-blind randomised controlled trial design. The training intervention will involve participation in an OFE programme implemented over 8 weeks, two sessions/week. Rating of perceived exertion, heart rate, training volume and adherence to the exercise programme will be registered each session. The control group will not receive any structured exercise programme. Blinded examiners will evaluate before and after the training programme muscle strength with both maximum knee extension and elbow flexion isometric tests, handgrip strength test and five time sit-to-stand test; cardiovascular fitness with 400-metre walking test; postural stability with the balance tests of the short physical performance battery (SPPB) battery; dynamic balance with Timed Up and Go (TUG) test; body composition with dual-energy X-ray absorptiometry; functional performance by gait speed, TUG and SPPB battery; blood pressure; and sagittal spine disposition and pelvic tilt. Information will also be collected about demographic characteristics, health-related quality of life, satisfaction with life and adherence to the Mediterranean diet questionnaires. After that, sarcopenia, osteoporosis and fracture risk will be calculated. The results derived from this research will increase the knowledge of the effectiveness of OFE training for improving the health of healthy community-dwelling middle and older adults.

WHAT IS ALREADY KNOWN ON THIS TOPICOutdoor fitness programmes can have health benefits for middle-aged and older adults in relation to muscle strength, cardiovascular capacity, postural stability and body composition. However, few studies have examined the benefits of outdoor fitness equipment training for older adults.WHAT THIS STUDY ADDSThis study provides evidence of the effectiveness of an outdoor fitness equipment training programme in improving specific health-related variables in a randomised controlled trial.HOW THIS STUDY MIGHT AFFECT RESEARCH, PRACTICE OR POLICYThis study proposes a detailed protocol to evaluate the effects of outdoor exercise equipment training in a specific population. The results could be substantial in the development of more effective and accessible interventions and the promotion of active and healthy lifestyles among older adults.

## Introduction

Practicing consistent physical activity is crucial to uphold optimal health and stave off chronic conditions and the effects of ageing in the older population. According to the WHO, physical activity can reduce the likelihood of middle-aged and older people developing chronic diseases such as heart disease, stroke, diabetes, sarcopenia, certain types of cancer by approximately 30–40%, diseases whose incidence increases with increasing age.^1^

Among the different physical activity options for the prevention of the effects of ageing, resistance training has gained popularity in recent years. In this line, some researchers conclude that resistance and balance exercise, with or without nutritional intervention, are the most effective interventions for improving quality of life and physical function in older adults with sarcopenia.^2^

Public areas are ideal for encouraging physical activity and resistance training since they encompass green spaces and outdoor fitness equipment (OFE).^3^ Furthermore, engaging in outdoor physical exercises can improve pulmonary, cardiovascular, cognitive, musculoskeletal and overall systemic health.^4^ Despite this, few studies have examined the benefits of OFE training for older adults.^5^ A recent review demonstrates that OFE training programmes have the potential to improve cardiovascular health, muscle strength, flexibility and balance and reduce falls while improving quality of life, alleviating depression and anxiety and increasing self-esteem.^6^ However, the authors suggest that more rigorous research is needed to understand the psychophysiological and social effects on health comprehensively.

Therefore, OFE training may be a free, feasible and timely way to address various health-related aspects of the ageing process. However, to date, no studies have been found that have analysed the effects of planned OFE training on health in middle and older adults with a randomised controlled trial design. Thus, this project will investigate the effectiveness of an 8-week OFE programme on health parameters in middle and older adults, corresponding the present paper to the design of the study protocol in which it presents an ongoing randomised controlled trial to investigate the effects of a circuit resistance training intervention with OFE on relevant physical and psychosocial performance in healthy community-dwelling middle and older adults.

The hypothesis is that the OFE training for 8 weeks, twice per week, improves physical fitness, body composition, psychological state and prevention of the effects of ageing after the intervention period compared with the daily activities control group (CG).

## Materials and methods

### Study design and setting

This protocol describes an 8-week two-armed parallel single-blind randomised controlled trial with blinded examiners (NCT04958499). This study is designed considering the recommendations of Consolidated Standards of Reporting Trials 7 and Standard Protocol Items: Recommendations for Interventional Trials statements.^8^

Participants will be evenly and randomly divided between the training group (TG) and the CG. The overall study design is summarised in figure 1. The choice of this design is related to the main objective and facilitating the interpretation of the data with intragroup and intergroup.

**Figure 1 F1:**
[figure not shown]
Consolidated Standards of Reporting Trials flow diagram showing the flow of participants through each stage of the study.

### Ethics approval and dissemination

All participants will be informed about the study procedures and will give their approval through informed consent before inclusion. All data collected during the study will be confidential. All participants receive a final report with their results to know their values at baseline and the end of the study. The trial will be conducted following the Declaration of Helsinki, and the study has been approved by the institutional ethics committee of the Catholic University of Murcia (CE111908).

Based on previous studies, groups larger than 30 were required for the result to reliably characterise precision error or change during clinical monitoring.^9^ A dropout rate of 16% will be assumed based on previous studies,^10^ so a minimum of 35 participants will be included per group. The RStudio V.3.15.0 software will be used to calculate the sample size. The sample size and statistical power were established considering the SD (4.2) in the maximum voluntary isometric contraction (MVIC).^11^ A significance power of 95% (1-β=0.95) and a significance level of 0.05 will be considered. Ultimately, the sample consisted of a minimum of 60 participants per group. This resulted in an assumed error of 1.06.

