### Primary outcomes

#### Maximum muscular strength

Both maximum knee extension and elbow flexion strengths will be evaluated under the same isometric conditions. For the knee extension test, participants will be seated in a chair specifically designed for the measurement of isometric knee extension strength (ES-1295254) equipped with a force transducer (Musclelab, Ergotest, Norway), maintaining both a hip and knee angle at 90 degrees. Participants will be directed to exert maximum strength against a pad above their ankle joint. For the elbow flexion test, participants will stand upright, holding a bar with both hands in a supine position, with the elbow at a 90-degree angle. Participants will be directed to exert maximal strength against the bar.

Following a previous protocol, participants will sustain exertion for 2–3 s during both assessments.^13^ The software (Musclelab, Ergotest, Norway) will quantify the maximum voluntary isometric contraction and the rate of force development. Each participant will complete three trials for each assessment, and the best one will be used.

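### The 60 per group and the error of 1.06 match a one-group 95% confidence half-width, but the article presents them as 95% power

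*Protocol article*

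**What the plan says.** The sample size text stands in the protocol article under Ethics approval and dissemination. It first argues from precision: groups larger than 30, then 16% dropout, "so a minimum of 35 participants will be included per group". It then gives a second basis: "The sample size and statistical power were established considering the SD (4.2) in the maximum voluntary isometric contraction (MVIC"). The error rates follow: "A significance power of 95% (1-β=0.95) and a significance level of 0.05 will be considered". The result is "Ultimately, the sample consisted of a minimum of 60 participants per group", and the paragraph closes with "This resulted in an assumed error of 1.06".

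No between-group difference to be detected is stated. The hypothesis at the end of the Introduction is comparative: improvement "after the intervention period compared with the daily activities control group (CG"). The Statistical analysis section plans comparisons of change within and between groups by repeated-measures analysis of variance.

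**The concern.** A power calculation needs a target difference, and the paragraph has none. The only figure of that kind, 1.06, is given as something that resulted from the 60 per group. This suggests a precision calculation with a power label attached, and writing 1-β makes that label explicit.

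A reader would take from the paragraph that the trial has 95% power on its sizing outcome, with an error of 1.06. If both figures describe the mean of a single group, neither applies to the comparison that the trial is designed to make. The strength results would then be read against a power and a precision that the paragraph does not support.

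**Working it through.** **Inputs from the sample size paragraph:** SD 4.2, α 0.05, power 0.95, 60 per group, error 1.06. Allocation is 1:1 (Randomisation and allocation).

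**Assumptions:** two-sided testing, because the article does not state sidedness, and 60 per group analysed.

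**1. Reproducing the article's pair.** Half-width of a 95% confidence interval for one mean:

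- z(0.975) × SD/√n = 1.96 × 4.2/√60 = 1.063
- Inverted: (1.96 × 4.2/1.06)² = 60.3

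Both figures are recovered. The formula contains no β and no second group.

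**2. Trying formulas that include power.** With 1.06 as the difference, SD 4.2 as given, and z(0.95) = 1.645:

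- Two groups: 2 × ((1.96 + 1.645) × 4.2/1.06)² = 408.02, so 409 per group. One-sided: 340.
- One sample: ((1.96 + 1.645) × 4.2/1.06)² = 204. One-sided: 170.
- In the other direction, the one-sample difference detectable with 95% power at n = 60 is 3.605 × 4.2/√60 = 1.95, not 1.06.

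No formula that includes power and uses only the stated inputs comes near the pair (60, 1.06).

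**3. What 60 per group gives for the between-group comparison, if 4.2 is the SD of the analysed quantity.** The standard error of the difference is 4.2 × √(2/60) = 0.767.

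- 95% confidence half-width: 1.96 × 0.767 = 1.50. This is √2 times, or about 41% more than, the one-group figure.
- Difference detectable with 95% power: 3.605 × 0.767 = 2.76 by the normal approximation, 2.79 by the noncentral t (2.79/4.2 = 0.66 SD).
- Difference detectable with 80% power: 2.15 by the normal approximation, 2.17 by the noncentral t.
- Power at a difference of 1.06: about 28% by either method.

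**4. What changes if 4.2 is the SD of a level.** With two time points, the group-by-time test of a repeated-measures analysis of variance compares changes. The SD of a change is 4.2 × √(2(1 − r)), where r is the pre-post correlation. The article gives no r, so the values below are assumptions:

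| Assumed r | SD of change | Power at 1.06 (t) |
|---|---|---|
| 0.5 | 4.20 | 28% |
| 0.8 | 2.66 | 58% |
| 0.9 | 1.88 | 87% |
| about 0.93 | about 1.6 | about 95% |

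At r = 0.5 the SD of change equals 4.2, so step 3 applies unchanged.

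**The case against.** The strongest objection is that the article never claims 95% power for a difference of 1.06. It calls 1.06 an error and reports it as an output. This stands. A reader might infer that the trial is underpowered, with 28% power where 95% was promised, or that it should have enrolled 409 per group. The article does not support that reading: it sets no target difference, so no power at 1.06 is promised or missed, and 60 per group may be adequate for a difference that the investigators would consider important.

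A second objection is that the one-group interval is an inference. If 4.2 is a level SD, 60 and 1.06 can also be made to fit a calculation with 95% power: at a pre-post correlation of about 0.93 for a between-group comparison of changes, or about 0.86 for a within-group paired test. Within-group comparisons are part of the plan. This also stands, so it would be too strong to say that power cannot have entered the calculation. But both fits need a correlation that the article does not give, whereas the confidence-interval formula reproduces both figures without any further input.

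Third, sizing for precision is legitimate, and the paragraph opens on that footing. That is granted. The error lies in labelling the 95% as 1-β and in leaving the control group out of the precision figure.

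Finally, the paragraph gives no unit for 4.2 and does not say which of the two isometric tests (knee extension or elbow flexion) it belongs to. A condensed article may leave such detail to the full protocol, and it carries no weight here. The main point is different in kind, because the article does print a power, an SD, a group size and an error, and as printed they do not fit together.

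**Conclusion.** The paragraph misdescribes its own calculation. On the stated inputs, 60 and 1.06 are the size and half-width of a one-group 95% confidence interval. The 95% is a confidence level reported as power, and 1.06 is not the precision of the training-versus-control difference.

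If 4.2 is the SD of the analysed quantity, 60 per group are analysed and the test is two-sided at 0.05, the half-width for that difference is about 1.50. Power is then 95% for a difference of 2.79 and 80% for 2.17. Power at 1.06 would be about 28%, but 1.06 is not a target that the protocol sets. If 4.2 is a level SD and changes are compared, power at 1.06 runs from 28% at r = 0.5 to 87% at r = 0.9 and reaches 95% near r = 0.93, all on assumed correlations.

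The finding is therefore a wrong statement of power and precision. It does not show that the trial is too small.

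**What to change.** Reword the paragraph and leave enrolment as it is:

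- Remove 95% power as the basis of the 60 per group.
- Describe 1.06 as the half-width of a 95% confidence interval for one group's mean.
- State what 60 analysed per group gives for the between-group comparison at two-sided 0.05 with SD 4.2: a half-width of 1.50, and detectable differences of 2.79 at 95% power and 2.17 at 80%.
- Say whether 4.2 is the SD of a level or of a change. If it is a level SD, state the assumed pre-post correlation and recompute these figures from it.

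The cost is one paragraph of text and no extra participants. With 4.2 as the SD of the analysed quantity, the stated precision becomes less favourable (1.50 in place of 1.06), and the 95% power is tied to a difference of 2.79.

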### Randomisation and allocation

After baseline measurements, participants will be randomly assigned to the TG or CG. A research team member will create a randomisation sequence (1:1) before the trial begins. The investigators who will conduct the assessments are not aware of which group the participants belong to, and participants will be instructed not to disclose the group to which they had been assigned.

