## Statistical analysis

The qualitative variables will be summarised in frequency. In contrast, the quantitative variables will be summarised using mean and SD for the TG and CG across the assessment time points. To ensure rigorous statistical evaluation, special attention has been given to controlling the type I (alpha) error and Bonferroni’s correction will be used to achieve p=0.005 for statistical significance. To compare characteristics between and within groups, the principle of intention to treat will be applied, with adjustments made to adhere to the exercise programme. The following tests will be employed to assess baseline characteristic differences between the two groups: Student’s t-test for parametric numerical variables, Mann-Whitney test for non-parametric variables and χ^2^ test for categorical binary variables.

To compare changes within and between the TG and CG across baseline and follow-up assessments, the subsequent tests will be used: for variables exhibiting normal distribution, repeated measures analyses of variance. Given the multiple comparisons involved, post hoc analyses will be conducted using t-tests with Sidak corrections to control the type I error rate; for non-parametric variables, the Friedman test will be followed by the Wilcoxon test, and, to address the multiple comparisons, the Bonferroni correction will be applied.

SPSS V.25.0 statistical software will be used in all the analyses. A p value<0.05 will be used to determine significant differences; however, this will be adjusted appropriately in the presence of multiple comparisons, as detailed above.

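### The stated 95% power is tied to no between-group difference; the 1.06 printed beside it matches the confidence-interval half-width of one group's mean

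*Protocol article*

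**What the plan says.** The sample-size text is in the protocol article under Ethics approval and dissemination. It starts from a rule of more than 30 per group, assumes 16% dropout, and concludes "so a minimum of 35 participants will be included per group". It then turns to an SD of 4.2 for MVIC, giving neither units nor whether this is the SD of a single measurement or of a change. It adds: "A significance power of 95% (1-β=0.95) and a significance level of 0.05 will be considered". It closes with "Ultimately, the sample consisted of a minimum of 60 participants per group. This resulted in an assumed error of 1.06".

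No difference between the training group and the control group is given as the target, and no formula is named.

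The hypothesis at the end of the Introduction is improvement relative to the control group, and allocation is 1:1 (Randomisation and allocation). The Statistical analysis section says a Bonferroni "correction will be used to achieve p=0.005 for statistical significance". It also gives p<0.05 as the general criterion, to be adjusted for multiple comparisons.

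**The concern.** A power statement needs an effect, a variance, an alpha and a sample size. This one has the last three and lacks the first. The only number that could be mistaken for an effect, 1.06, is described as an error that results from the sample size. On checking, it behaves as a precision figure for one arm, so the 95% appears to have served as a confidence level while being reported as power.

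MVIC is among the primary outcomes. If the text stands, readers cannot tell which between-group difference the trial could reliably detect. A non-significant MVIC result could then be read as evidence of no effect when the trial was sensitive only to differences well above 1.06.

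**Working it through.** **Inputs.** From the sample-size paragraph: SD 4.2, power 0.95, alpha 0.05, n = 60 per group, error 1.06, dropout 16%. From Statistical analysis: alpha 0.005. My assumptions: two-sided tests, and 4.2 as the SD of the value analysed.

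**1. Reproducing the plan's figure.** The 95% confidence-interval half-width for one mean is 1.96 × SD / √n:
- 1.96 × 4.2 / √60 = 1.063, against the stated 1.06.
- Inverted: (1.96 × 4.2 / 1.06)² = 60.3, against the stated 60.

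**2. Trying power formulas instead.** The sample size for a difference of 1.06 with SD 4.2, 95% power and alpha 0.05 would be:
- two groups: 409 per group two-sided, 340 one-sided;
- one sample or paired: 204 two-sided, 170 one-sided.

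At 80% power the two-group figures are 247 and 195. None of these gives 60.

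**3. Precision for the comparison the trial makes.** The between-group half-width is 1.96 × SD × √(2/n) = 1.96 × 4.2 × √(2/60) = 1.50. With 50 per group it is 1.65.

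**4. Difference detectable with 95% power.** The normal approximation is (z for alpha + z for power) × SD × √(2/n). For n = 60 and alpha 0.05 this is (1.960 + 1.645) × 4.2 × √(2/60) = 2.76. The noncentral t distribution gives slightly larger values, used from here on. The 50 comes from 60 × 0.84 = 50.4, and applies if 60 are randomised and 16% are lost.

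| Analysed per group | alpha 0.05 | alpha 0.005 |
|---|---|---|
| 60 | 2.79 | 3.47 |
| 50 | 3.06 | 3.82 |

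In SD units, 2.79 / 4.2 = 0.66.

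**5. Conditional check: power if 1.06 were the target.** The standard error of the difference is 4.2 × √(2/60) = 0.767, so the noncentrality is 1.06 / 0.767 = 1.38. Two-sided t-test power is 28% at alpha 0.05 and 7% at 0.005. With 50 per group it is 24% and 6%.

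**6. Sensitivity to the meaning of 4.2.** If 4.2 is a cross-sectional SD and change scores are analysed, the change SD is 4.2 × √(2(1 − r)), where r is the pre-post correlation. The document gives no r, so the values below are assumptions. Power for 1.06 with 60 per group at alpha 0.05:

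| r | Change SD | Power |
|---|---|---|
| 0.5 | 4.20 | 28% |
| 0.7 | 3.25 | 42% |
| 0.8 | 2.66 | 58% |
| 0.9 | 1.88 | 87% |

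An r of about 0.93 would be needed for 95%.

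**The case against.** The strongest reply is that the protocol never calls 1.06 a difference to be detected. It is presented as an output of the sample size ("This resulted in an assumed error of 1.06"), in a paragraph that opens with a precision aim. A reader might infer that the trial claims 95% power for 1.06 and really has 28%, or 7% at 0.005. The document does not support that reading: it makes no such claim, so those percentages answer a question the plan did not pose. They also depend on what 4.2 is, as step 6 shows. This part of the objection stands, and the percentages are kept only as conditional figures.

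It is also fair that no formula is named. The single-mean origin of 60 and 1.06 is inferred from a close numerical match, not documented.

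A reader might also conclude that the enrolment target contradicts itself, with 35 and 60 both given as minimums. That is too strong. The wording "Ultimately, the sample consisted of a minimum of 60 participants per group" marks 60 as the operative figure, and 60 satisfies a floor of 35. The shortfall in the 35 (30 / 0.84 = 35.7) has no consequence once 60 governs. What remains is untidiness, plus the absence of any visible dropout allowance on the 60.

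Finally, because Statistical analysis states both 0.005 and p<0.05, the alpha that will govern MVIC is not settled. The 0.005 results are therefore one of two cases.

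None of this rescues the power statement. If 1.06 is a precision figure, the 95% power has no effect attached to it at all.

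**Conclusion.** The point holds as a statement about unsupported power. The article prints an SD, a power, an alpha, a sample size and a result as if they belonged together. The result fits a one-group precision calculation in which power plays no part. This is not detail left to a fuller document, since the inputs and the result are both on the page and do not fit.

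The size of the problem is best expressed by the detectable differences in step 4, which do not depend on how 1.06 is read: from 2.79 to 3.82, according to the alpha and the number analysed. They do rest on 4.2 being the SD of the analysed value and on a two-sided two-sample t-test. If 4.2 is cross-sectional and change is analysed, they would shrink for a pre-post correlation above 0.5 and grow for one below it.

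**What to change.** Keep the enrolment and rewrite the paragraph:

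1. State the units of 4.2 and whether it is the SD of a single measurement or of a change.
2. Give 60 as the only minimum, and say whether it means randomised or completing. Apply the 16% dropout to it: 60 randomised leaves about 50, whereas 60 completing implies 60 / 0.84 = 71.4, so 72 randomised per group.
3. Replace the power sentence with the between-group MVIC difference detectable with 95% power at the alpha the analysis will use. For an analysed SD of 4.2 this is 2.79 (60 analysed per group) or 3.06 (50) at alpha 0.05, and 3.47 or 3.82 at alpha 0.005. Settle which alpha governs MVIC so that the two sections agree.
4. Delete 1.06, or label it as the 95% confidence-interval half-width of a single group's mean at n = 60.

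The cost is the rewording of one paragraph. No participants are added if 60 is the number randomised. The drawback is a less favourable stated sensitivity.
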